### Blinding

In this trial, investigators will not be in contact with the CRC, the clinical pharmacist, or the statistician. The success of blinding will be assessed at each participant's last visit. Researchers who are blinded to the allocation results will perform the outcome assessment. The blinding procedure will also be verified by the authorised CRO.

### Treatment protocol

Participants will receive Hwangryunhaedoktang or a placebo-drug for eight weeks. Oral administration occurs according to the following statement:

Patients in group 1 will receive Hwangryunhaedoktang and instructions on how to make the tea; they should consume a packet of the medicine (5.00 g) with tepid water three times a day 30 minutes after meals.

Patients in group 2 will receive the placebo medicine (powdered extract), used in the same way as in group 1.

The defined daily doses (DDDs) of these herbal medicines should be determined based on the specifications and analytical procedures of drug products in KFDA guidelines. However, no pilot study has been reported so far.

#### Experimental medicines (Hwangryunhaedoktang)

Hanpoong Pharm and Foods Co., Ltd., produced the Hwangryunhaedoktang and the placebo medicine according to Korea Good Manufacturing Practice (KGMP) standards.

Hwangryunhaedoktang used in this trial is a brown, bitter herbal extract. Hwangryunhaedoktang is composed of four herbs: Powdered extract of Scutellaria baicalensis (334.00 mg as Baicalin), 1.67 g; Powdered extract of Gardenia jasminoides, 1.67 g; Powdered extract of Coptis chinensis (116.20 mg as Berberine), 0.83 g; Powdered extract of Phellodendron Amurense (19.92 mg as Berberine), 0.83 g.

#### Placebo medicine

Hanpoong Pharm and Foods Co., Ltd., developed a homogenous powdered extract of brown colour, which was made by mixing 3.489 g of lactose, 1.495 g of starch, and 0.016 g of pigments approved by KFDA. The colour, form, weight, odour, and taste of the placebo are very similar to the treatment medicines.

### Primary outcome measurement

SCORAD index will be used as the primary outcome variable. SCORAD is a clinical tool for assessing the severity of AD as objectively as possible. SCORAD consists of three scales: extent, intensity, and subjective. The severity of eruptions on lesions is evaluated on a 4-point scale (0: none, 1: mild, 2: moderate, 3: severe) by scoring the erythema, oedema, oozing, excoriation, lichenification, and xerosis. SCORAD is calculated by the equation A/5 + 7 × B/2 + C. In this equation, A is the percentage of body area with a skin rash, B is the total score of erythema, oedema, oozing, excoriation, lichenification, and xerosis, each of which was evaluated on a 4-point scale, and C is the visual analogue scale (VAS, a scale from 0 to 10) for subjective assessment of both itching and sleep loss[18-20]. It will be measured at treatment initiation, at two weeks after the first medication administration, at four weeks after the first medication administration, and at eight weeks after the first medication administration.

### Secondary outcome measurement

Secondary outcome measurements include the total IgE and eosinophil counts. These will be measured at treatment initiation, at four weeks after the first medication administration, and at eight weeks after the first medication administration. The EuroQoL 5-Dimension (EQ-5D), the Health Utilities Index Mark 3 (HUI3), and the Dermatology Life Quality Index (DLQI) will be measured at treatment initiation and at eight weeks after the first medication administration, as a measure of health outcomes. The data collection schedule is detailed in Table 1.

**Table 1 T1:** Data Collection Schedule

Period	Screening	Treatment period				Followup
**Visit**	**1st** **(D -7)**	**2nd** **(D 1)**	**3rd** **(D 15)**	**4th** **(D 29)**	**5th** **(D 57)**	**(D 71)**

Informed consent	◯					

Demographic characteristics	◯					

Medical History	◯					

Safety Assessment	◯	◯	◯	◯	◯	

Total IgE, Eosinophil count		◯		◯	◯	

SCORAD Index		◯	◯	◯	◯	

Dermatology Life Quality Index		◯			◯	

EQ-5D		◯			◯	

Health Utilities Index Mark 3		◯			◯	

Adverse effects			◯	◯	◯	◯

Blinding Assessment					◯	

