### Sample size

We wished to estimate the sample size that would be sufficient to detect significant differences in the SCORing Atopic Dermatitis (SCORAD) index between the experimental and control groups. Sample size was determined prospectively, as described in a previous study[16,17]. The mean and standard deviation of expected difference scores in SCORAD were 13 and 20 between the experimental and control group. The following formula was used to estimate the sample size for a two-group trial:

$$\frac{2{\left(Z_{\alpha ∕2}+Z_{\beta }\right)}^{2}\sigma^{2}}{{\left(\mu_{c}-\mu_{t}\right)}^{2}}$$

Calculations were performed using 80% power, a 5% significance level, and a 25% dropout rate. The required sample size was approximately 37 participants for each group. We plan to enrol 100 participants in each of the two groups, allowing for a 25% withdrawal rate.

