### Statistical analysis

Analyses will be performed for two populations: 1) an intention-to-treat population consisting of all randomised participants who have at least one measurable outcome report following treatment (missing data are replaced with the last observation values) and 2) a per-protocol population including only participants without major protocol deviations. All data will be descriptively analysed. All main analyses will be based on the intention-to-treat population and conducted using LOCF (last observation carried forward) imputation method. For primary outcome measures, the mean differences from baseline values to the end of treatment will be compared using a independent T-test (Expected noncentrality parameter = 2.87, Critical t = 1.99, Power = 0.80). Paired T-test or non-centrality Wilcoxon rank sum test will be used for comparing safety variables. Repeated measure ANOVA (analysis of covariance) or repeated measure ANCOVA tests will also be performed for within-group and between-group analyses. Baseline data will be collected on each participant at randomisation in trial can be used to describe the population of patients, to assess comparability of treatment groups, to achieve balanced randomisation, to adjust possible comfoundings for prognostic factors, and to undertake subgroup analyses. We will exercise caution when drawing conclusions from subgroup findings.

Statistical analyses will be performed using the STATA statistical package program (ver. 11.0), and the level of significance is established at α = 0.05.

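### DLQI, EQ-5D and HUI3 have no measurement between day 1 and day 57, so carrying the last observation forward can only give an intention-to-treat participant without the day-57 questionnaire a change of zero

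*Protocol article*

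**What the plan says.** The section Secondary outcome measurement schedules the three quality-of-life instruments twice: they "will be measured at treatment initiation and at eight weeks after the first medication administration, as a measure of health outcomes". Table 1 agrees, with marks at day 1 and day 57 only. The other outcomes have interim values. For total IgE and eosinophils, "These will be measured at treatment initiation, at four weeks after the first medication administration, and at eight weeks after the first medication administration". For SCORAD, "It will be measured at treatment initiation, at two weeks after the first medication administration, at four weeks after the first medication administration", and again at eight weeks.

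The Statistical analysis section defines the intention-to-treat population as "all randomised participants who have at least one measurable outcome report following treatment (missing data are replaced with the last observation values"). It then adds: "All main analyses will be based on the intention-to-treat population and conducted using LOCF (last observation carried forward) imputation method". The Sample size section plans for loss: "Calculations were performed using 80% power, a 5% significance level, and a 25% dropout rate".

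On blinding, the text says: "The success of blinding will be assessed at each participant's last visit". Table 1 places that assessment at day 57 only.

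**The concern.** The imputation rule needs something to carry. SCORAD has values at days 15 and 29, and the blood measures have one at day 29. The three questionnaires have nothing after day 1. A participant who leaves after day 15 or day 29 has a post-treatment SCORAD and so qualifies for the intention-to-treat set, but the only quality-of-life score on file is baseline. The rule then records no change at week 8, although nothing was measured on treatment.

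Zero is not a neutral value. Participants are told to stop other treatments for their dermatitis for the whole study, so leaving because of worsening or lack of response is plausible, and such a person would be scored as unchanged. When loss is equal between arms, the zeros dilute the comparison. When it is unequal, they can produce a difference that reflects only who left. The article says that it will assess change in quality of life and that the results could support later economic evaluation, and the two utility measures share this schedule.

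An analysis plan can replace the imputation, but it cannot recover questionnaires that were never given. That is why the point belongs with the visit schedule.

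**Working it through.** **The plan's own figure.** The article gives no sample-size figure for quality of life, so the check starts from the SCORAD calculation, which supplies the group size and dropout rate. Inputs from the Sample size section: difference 13, SD 20, two-sided 5%, power 80%.

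- n per group = 2 × (1.960 + 0.842)² × 20² / 13² = 37.15. The article states about 37, so the figure reproduces.
- Allowing for 25% dropout: 37 / 0.75 = 49.3, or 50 per group and 100 in total. This matches the total in Randomisation and allocation. The Sample size section says 100 in each group, which is a separate inconsistency. I use 50 per group.

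**How many receive the baseline score.** Expected leavers per group: 0.25 × 50 = 12.5. Those who leave before day 15 normally have no post-treatment outcome and fall outside the set. The timing of dropout is not given, so the whole range is shown.

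| Share of leavers gone before day 15 | Imputed per group | Set per group | Share imputed |
|---|---|---|---|
| 0 | 12.5 | 50 | 25% |
| one half | 6.25 | 43.75 | 14.3% |
| all | 0 | 37.5 | 0% |

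**Effect on the group difference.** Let mA and mP be the mean changes among completers (active, placebo), and pA and pP the imputed shares. Each imputed change is zero, so the reported difference is (1 − pA) × mA − (1 − pP) × mP. To read any departure from mA − mP as bias, one must assume that leavers would have changed as completers did. The DLQI changes and the unequal dropout rates below are illustrative assumptions. Negative means improvement.

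- Equal loss, mA = −5, mP = −2, 25% imputed in each arm: 0.75 × (−5) − 0.75 × (−2) = −2.25, against −3. The ratio is 0.75.
- The same with 14.3% imputed: 0.857 × (−3) = −2.57.
- No drug effect (−4 in both arms), 15% lost on active and 35% on placebo, all after day 15: 0.85 × (−4) = −3.4 and 0.65 × (−4) = −2.6, a difference of −0.8 where there is none.
- The same with half of each arm's leavers gone before day 15: 42.5/46.25 × (−4) = −3.68 and 32.5/41.25 × (−4) = −3.15, a difference of −0.52.

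**On a standardised scale.** Borrowing 13/20 = 0.65 from SCORAD as an assumed completer effect, with nobody leaving before day 15 and a placebo change between 0 and 0.325 SD:

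- Equal 25% loss: the effect falls to 0.49. Approximate power is 0.75 to 0.78, against 0.80 for a completer comparison with 37.5 per group.
- 35% lost on active, 15% on placebo: 0.36 to 0.42, that is 55% to 65% of the completer effect.
- 15% lost on active, 35% on placebo: 0.55 to 0.62, that is 85% to 95%.

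With equal loss the cost in power is therefore small. The larger effects are on the size of the estimate and under unequal loss.

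**The other reading of the set.** If the entry condition is applied to each outcome separately, nobody without a day-57 questionnaire enters the quality-of-life analysis. Nothing is imputed, and the comparison has 37.5 completers per group under the planned loss.

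**The case against.** Several counter-arguments are sound and limit the point.

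- A reader might infer that everyone who stops early is given the baseline score. The documents do not support that. Leavers before day 15 are normally outside the set, and someone who stops the medicine but attends day 57 has an observed score.
- A reader might also infer that about 25 of 100 participants will contribute an unmeasured zero. That is the top of the range and needs every loss to fall after day 15. The 25% is also a planning allowance, not a forecast of missing questionnaires, and the article gives no split by arm.
- The text does not say whether the entry condition means any outcome or the one being analysed, and it names the t-test only for the primary outcome. The extension of the imputation rule to secondary outcomes is implied by the definition of the set, not spelled out.
- If leavers drift back towards baseline, zero is nearly right for them and there is little dilution.
- The absence of an early-withdrawal column in Table 1 does not show that no such assessment exists. The article condenses a fuller protocol.
- On blinding, the text and Table 1 agree for anyone who completes the schedule, because the day-71 contact is a phone call. They part only for those who withdraw.

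What remains is the combination that the article does fix: two time points, and a rule that replaces missing values in the set with the last observation. The per-outcome reading does not rescue it, since it leaves a completers-only comparison under an intention-to-treat label.

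**Conclusion.** The point holds for participants who are in the intention-to-treat set and lack the day-57 questionnaire. For them, on the natural reading of the Statistical analysis section, the carried-forward quality-of-life score can only be the baseline score. At the planned dropout this is between 0 and 25% of the set, depending on how many leave before day 15. The shrinkage to 75% and the spurious −0.8 are illustrations for the top of that range. They rest on assumed changes, on assumed dropout rates by arm in the second case, and on leavers resembling completers.

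The matter is confined to three secondary outcomes, with a minor mismatch in the blinding check. It does not touch SCORAD, which has interim values. It should be corrected, chiefly because the missing data cannot be collected afterwards.

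**What to change.** 1. Unless the full protocol already provides for it, add a column to Table 1 for participants who withdraw, and give DLQI, EQ-5D and HUI3 at their last attended visit. Any carried-forward value would then be one obtained after treatment began.
2. Invite those who withdraw to answer the three questionnaires at day 57 by phone or post. The trial already plans a phone contact.
3. State whether entry to the intention-to-treat set is judged on any outcome or on the outcome analysed.
4. Make observed day-57 scores, adjusted for baseline, the main quality-of-life analysis. Say that this assumes missingness is explained by arm and baseline, so it does not by itself remove selection by who left. Keep the carried-forward version as a sensitivity analysis, and report by arm how many values are carried from baseline.
5. Minor: align Table 1 with the Blinding section, so that the blinding question is also asked at the last visit of those who withdraw.

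The cost is one table column, a few sentences in the analysis section and a few minutes for each person who withdraws, at most about 25 people under the planned rate. Some will not respond.

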### Patient safety

All patients will undergo routine testing that included the following: complete blood cell count (CBC), erythrocyte sedimentation rate (ESR), and blood chemistry, as well as PA chest film and urine analysis before randomisation and immediately after completing the treatment. Vital signs will be measured at every visit. These tests help to identify and exclude patients with serious liver and kidney disease as well as those with other severe illness. Investigators will assess a significant result in these tests according to explicit criteria defining the incidence and intensity of adverse events. Also a causality evaluation of adverse drug reactions will be discussed.

### Statistical analysis

Analyses will be performed for two populations: 1) an intention-to-treat population consisting of all randomised participants who have at least one measurable outcome report following treatment (missing data are replaced with the last observation values) and 2) a per-protocol population including only participants without major protocol deviations. All data will be descriptively analysed. All main analyses will be based on the intention-to-treat population and conducted using LOCF (last observation carried forward) imputation method. For primary outcome measures, the mean differences from baseline values to the end of treatment will be compared using a independent T-test (Expected noncentrality parameter = 2.87, Critical t = 1.99, Power = 0.80). Paired T-test or non-centrality Wilcoxon rank sum test will be used for comparing safety variables. Repeated measure ANOVA (analysis of covariance) or repeated measure ANCOVA tests will also be performed for within-group and between-group analyses. Baseline data will be collected on each participant at randomisation in trial can be used to describe the population of patients, to assess comparability of treatment groups, to achieve balanced randomisation, to adjust possible comfoundings for prognostic factors, and to undertake subgroup analyses. We will exercise caution when drawing conclusions from subgroup findings.

Statistical analyses will be performed using the STATA statistical package program (ver. 11.0), and the level of significance is established at α = 0.05.

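### The primary SCORAD comparison relies on LOCF while 25% withdrawal is allowed for, so the week-8 difference depends on the timing and balance of withdrawal as well as on treatment

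*Protocol article*

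**What the plan says.** The Statistical analysis section of the protocol article sets the rule for incomplete data itself: "All main analyses will be based on the intention-to-treat population and conducted using LOCF (last observation carried forward) imputation method". The analysis set is "an intention-to-treat population consisting of all randomised participants who have at least one measurable outcome report following treatment", and for the primary outcome "the mean differences from baseline values to the end of treatment will be compared using a independent T-test".

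The section adds two further analyses. One uses "a per-protocol population including only participants without major protocol deviations". The other is longitudinal: "Repeated measure ANOVA (analysis of covariance) or repeated measure ANCOVA tests will also be performed for within-group and between-group analyses". Neither comes with a missing-data rule of its own, and no reason is given for choosing LOCF.

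On the schedule of SCORAD, the Primary outcome measurement section says "It will be measured at treatment initiation, at two weeks after the first medication administration", and then at four and eight weeks. Table 1 agrees (days 1, 15, 29 and 57).

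On expected losses, the Sample size section says: "Calculations were performed using 80% power, a 5% significance level, and a 25% dropout rate".

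**The concern.** With SCORAD at baseline and weeks 2, 4 and 8, and an analysis set that requires an outcome after treatment has started, a week-8 SCORAD filled in for someone who has left is a week-2 or week-4 score. LOCF is right on average only if the leavers' mean would not have changed after that visit. The article gives no reason to expect this: it describes the disease as chronic and relapsing, treatment runs for eight weeks, and participants are told to stop other treatments for it.

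Two consequences follow. First, the week-8 mean of each arm becomes a mixture of week-8 and earlier means, with weights set by that arm's withdrawal. The estimate can therefore be off even when withdrawal has nothing to do with outcome. Second, the t-test treats the filled-in scores as real week-8 observations and ignores the uncertainty about them.

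What is at stake is the trial's single primary estimate. Recruiting extra participants to allow for withdrawal restores numbers but does not remove this bias.

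**Working it through.** **The plan's own figure first.** Inputs from the Sample size section: difference 13, SD 20, 80% power, 5% significance (two-sided, since the Statistical analysis section gives a critical t of 1.99).

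- n per group = 2(1.96 + 0.8416)² × 20² / 13² = 37.15, which agrees with the stated figure of about 37.
- Allowing for 25% withdrawal: 37 / 0.75 = 49.3, so 50 per group and 100 in total.

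The Randomisation and allocation section gives 100 in total, but the Sample size section says 100 in each group. These two statements must be reconciled. I use 50 per group below because it follows from the calculation.

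**Assumptions that are not in the documents.**

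- Mean SCORAD change at weeks 2/4/8 is -8/-14/-23 on active and -4/-7/-10 on placebo. The true week-8 difference is then 23 - 10 = 13, the planned value.
- Leavers follow the same mean course as those who stay. Their last visit is split evenly between weeks 2 and 4.
- SD stays at 20.

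**Formula.** With withdrawal proportion d in an arm:

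LOCF mean = (1 - d) × week-8 mean + d × (week-2 mean + week-4 mean)/2

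The carried-forward mean is (-8 - 14)/2 = -11 on active and (-4 - 7)/2 = -5.5 on placebo.

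**With a true difference of 13.** Power uses the noncentral t with noncentrality = difference / (20 × √(2/50)) = difference / 4.

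| Withdrawal, active / placebo | Active mean | Placebo mean | LOCF difference | Power |
|---|---|---|---|---|
| none | -23 | -10 | 13 | 0.90 |
| 25% / 25% | 0.75(-23) + 0.25(-11) = -20.0 | 0.75(-10) + 0.25(-5.5) = -8.875 | 11.1 | 0.79 |
| 35% / 15% | 0.65(-23) + 0.35(-11) = -18.8 | 0.85(-10) + 0.15(-5.5) = -9.325 | 9.5 | 0.65 |
| 15% / 35% | 0.85(-23) + 0.15(-11) = -21.2 | 0.65(-10) + 0.35(-5.5) = -8.425 | 12.8 | 0.89 |

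With equal 25% withdrawal, LOCF keeps 11.125/13 = 86% of the difference.

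**With no true effect.** If both arms follow the same course, the false difference is (d₁ - d₂) × (week-8 change - carried-forward change), with changes taken as sizes.

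- Equal withdrawal: d₁ - d₂ = 0, so there is no false difference and the rejection rate stays at 5%.
- 35% versus 15%, both arms on the placebo course: 0.20 × (10 - 5.5) = 0.9 points, rejection about 5.6%.
- 35% versus 15%, both arms on the active course: 0.20 × (23 - 11) = 2.4 points, rejection about 9%.

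Because everyone is improving in this illustration, the arm that loses more people looks worse.

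**Other assumed courses.** Suppose 25% and 50% of the week-8 change is reached by weeks 2 and 4 (slow), or 60% and 85% (fast), with any split of last visits.

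- 25% withdrawal in both arms gives 10.6 to 11.4 (slow) or 11.7 to 12.5 (fast).
- Unequal withdrawal, up to 40% against 10%, with mean changes of 23 and 10, gives 6.9 when more leave active and 14.3 when more leave placebo.

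The size of the bias thus depends heavily on the course and on the imbalance.

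**The case against.** Several things can fairly be said for the plan.

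- A reader might infer that the week-8 result would reflect withdrawal instead of treatment. The figures do not support that. If withdrawal is near the planning allowance, about three quarters of participants are observed at week 8, and 86% of the difference survives in the equal-withdrawal case.
- A reader might infer that LOCF will manufacture an effect. With equal withdrawal and equal mean courses it does not: it dilutes a true effect and leaves a null result at 5%. A false difference here needs unequal withdrawal or unequal courses among leavers.
- One might argue that the bitter active product will drive people out of that arm. The article says the placebo is very similar in taste, and nothing in it predicts which arm will lose more.
- A reader might take the worst case to be leavers who carry none of the effect: 13 × 0.75 = 9.75, power about 0.67. The analysis set excludes people with no outcome after treatment, so this is not the natural reading. In the illustration leavers carry 5.5 of 13 points, and power of about 0.79 is close to the planned 0.80.
- The 25% is a planning allowance, not a forecast or a ceiling, and the earliest leavers are excluded rather than imputed.
- Sensitivity analyses, covariates and covariance structure may be in an analysis plan that is not shown, and an article may condense them.

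All of this stands and limits the size of the point. It does not remove it. The primary imputation rule is written in this document, so an unseen analysis plan does not excuse it. The repeated-measures analysis is supplementary, and if it counts as a main analysis it falls under the same LOCF rule.

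**Conclusion.** The point holds as a weakness of the stated primary method, and it should be fixed. LOCF makes the primary estimate depend on the timing and balance of withdrawal as well as on treatment, and the document names no analysis under another missing-data assumption.

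Under the assumed courses, the cost with equal 25% withdrawal is about 1.9 of 13 points, and power falls from 0.90 to about 0.79. With 35% against 15% the estimate is 9.5 or 12.8, depending on which arm loses more. Under no effect, that imbalance gives 0.9 to 2.4 false points and rejection of about 5.6% to 9%.

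These figures rest on assumed trajectories, an even split of last visits, an unchanged SD and 50 per group. With 100 per group the bias in points is the same but power is higher: for 11.125 the noncentrality is 11.125 / (20 × √(2/100)) = 3.93, giving power of about 0.97. Serious distortion needs unequal or outcome-related withdrawal, which the documents neither predict nor rule out.

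**What to change.** Make the primary analysis a prespecified likelihood-based repeated-measures model of SCORAD at weeks 2, 4 and 8. Include treatment, visit, treatment-by-visit and baseline SCORAD, take the week-8 treatment contrast as the estimate, and use no single imputation. Multiple imputation would be an acceptable alternative. This model would replace the open choice between repeated-measures ANOVA and ANCOVA. Keep LOCF only as a sensitivity analysis. Settle the wording before unblinding, because the method cannot credibly be changed once withdrawal by arm is known. In the same revision, reconcile the two statements of planned enrolment.

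The cost is a change of text and modest extra programming, with no new visits, data or participants. The downside is reliance on a missing-at-random assumption: the model removes the bias when withdrawal is random or explained by the observed scores, but not when it depends on unobserved ones.

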### Randomisation and allocation

The randomisation procedure will be guaranteed by the authorised Clinical Research Organisation (CRO). An expert on statistics from CRO who have no contact with the study participants will conduct the randomisation of participants. Participants will be assigned random numbers via random number generator program (Microsoft Office Excel 2007). Random numbers will be sent to each centre, and randomisation table will be kept blinding by CRO during the research period. Ultimately, 100 participants will be randomised into the two groups at the two centres. However, the number of subjects planned for each location is not fixed. Opaque sealed envelopes containing serial numbers will be delivered to each centre. Opaque sealed randomisation table kept by CRO should be opened as a Standard Operating Procedure (SOP). If it has to be opened in urgent situation dealing with serious adverse events, primary investigator must report that to the CRO. Before the random assignment, all participants will be informed that they would be allocated to one of two groups. Random allocation will be conducted at the second visit. Random numbers with their corresponding participants will be determined by the order of the time of second visit. The allocation results will not be announced to the participants until the last visit of the last randomised participant.

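### The primary t-test on change in SCORAD is valid, but prespecified adjustment for baseline SCORAD would give a more precise estimate that is less exposed to chance imbalance, at no cost in data

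*Protocol article*

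**What the plan says.** The Statistical analysis section of the protocol article settles the primary test: "the mean differences from baseline values to the end of treatment will be compared using a independent T-test". It attaches that test's own power figures ("Expected noncentrality parameter = 2.87, Critical t = 1.99, Power = 0.80") and names no covariate.

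The Sample size section gives the planning values: "The mean and standard deviation of expected difference scores in SCORAD were 13 and 20 between the experimental and control group" and "Calculations were performed using 80% power, a 5% significance level, and a 25% dropout rate". The result is "The required sample size was approximately 37 participants for each group".

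According to the primary outcome section, Table 1 and the Randomisation and allocation section, SCORAD is scored at the second visit, which is also when allocation takes place. A baseline value should therefore exist for every randomised participant.

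Adjustment appears in two other places in the Statistical analysis section:
- A repeated-measures ANOVA or ANCOVA is listed as a further analysis, with no covariates named.
- Among the possible uses of baseline data is "to adjust possible comfoundings for prognostic factors".

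Neither is made primary.

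**The concern.** Subtracting baseline corrects fully for it only if the slope of final on baseline SCORAD is 1. With a smaller slope the subtraction over-corrects. An arm that starts worse by chance will then tend to show a larger fall, whatever the treatment does, and part of that gap stays in the treatment estimate. The same forced slope adds noise even when the arms are balanced.

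Analysis of covariance estimates the slope from the data, targets the same treatment difference and uses a measurement already collected. The eligibility criteria set no SCORAD range, so baseline severity may vary widely. At stake are the precision of the main result and how far it depends on the luck of allocation.

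**Working it through.** **Inputs from the article.** Difference 13 and SD 20 (Sample size; worded as difference scores, so taken here as the SD of change), two-sided 5%, 80% power, 25% dropout, and 37 per group.

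**Assumptions not in the article.** The correlation ρ between baseline and week-8 SCORAD is taken as 0.3, 0.5 and 0.7. The variance σ² is taken as equal at both times, and allocation as 1:1.

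**Step 1: reproduce the plan's figure.** n = 2(1.96 + 0.842)² × 20² / 13² = 37.15, which agrees with the stated 37 (38 if rounded up). With 37 analysed per group, the t-test has noncentrality (13/20)√(37/2) = 2.80 and power 0.79. The quoted noncentrality of 2.87 corresponds to 39 per group, (13/20)√(39/2), with power 0.81. That small mismatch does not affect this point.

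**Step 2: variance with and without adjustment.**
- Change score: 2(1 − ρ)σ²
- ANCOVA residual: (1 − ρ²)σ²
- Ratio: (1 + ρ)/2, so the residual SD is 20√((1 + ρ)/2)

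Without the equal-variance assumption, with SDs σ₀ at baseline and σ₁ at week 8, the change-score variance exceeds the ANCOVA variance by (σ₀ − ρσ₁)². This is never negative, so in large samples ANCOVA is never the less precise of the two.

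**Step 3: power for a difference of 13.**

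| | Unadjusted | ρ = 0.3 | ρ = 0.5 | ρ = 0.7 |
|---|---|---|---|---|
| Variance reduction | – | 35% | 25% | 15% |
| SD used | 20 | 16.1 | 17.3 | 18.4 |
| n per group for 80% power | 38 | 25 | 28 | 32 |
| Power, 37 analysed per group | 0.79 | 0.93 | 0.89 | 0.85 |
| Power, 50 analysed per group | 0.90 | 0.98 | 0.96 | 0.94 |
| Power, 100 analysed per group | >0.99 | >0.99 | >0.99 | >0.99 |

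A simulation at 37 per group (4,000 runs for each ρ), which includes the cost of estimating the slope, gave 0.79 for the t-test and 0.93, 0.89 and 0.84 for ANCOVA.

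**Step 4: what a chance baseline difference leaves behind.** With equal variances the slope equals ρ, so a baseline difference D moves the change-score estimate by (1 − ρ)D in size. The baseline SD implied by an SD of change of 20 is 20/√(2(1 − ρ)), and the standard error of D is that SD times √(2/n).

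| | ρ = 0.3 | ρ = 0.5 | ρ = 0.7 |
|---|---|---|---|
| Baseline SD | 16.9 | 20.0 | 25.8 |
| SE of D, 37 per group | 3.93 | 4.65 | 6.00 |
| Shift for a 1-SE imbalance, 37 per group | 2.8 | 2.3 | 1.8 |
| Same, 50 per group | 2.4 | 2.0 | 1.6 |

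These shifts are in SCORAD points, against a target difference of 13. ANCOVA removes them as far as the relation is linear.

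**Step 5: which sample size applies.** The Sample size section says "We plan to enrol 100 participants in each of the two groups, allowing for a 25% withdrawal rate". The Randomisation and allocation section says "Ultimately, 100 participants will be randomised into the two groups at the two centres". Only 100 in total follows from the calculation: 37/(1 − 0.25) = 49.3, or 50 per group. The rows for 37 and 50 are therefore the relevant ones if 100 is the total. If 100 per group is meant, the power gain largely disappears.

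**The case against.** The strongest reply is that nothing here is invalid. The test is prespecified, it is unbiased over randomisation, and it is the test for which the trial was sized. It reaches about 80% power without adjustment. A change score already uses baseline, so protection against imbalance is reduced, not absent. The remaining shift is small beside 13 points, and it exists only given an imbalance that has actually occurred. All of this stands, and it limits the point to efficiency and to the estimate given the observed baseline.

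It can also be said that adjustment is already planned and that its covariates are detail for an analysis plan that is not shown. The absence of a covariate list is indeed no finding. But the article itself fixes the primary test as unadjusted and makes the adjusted model an additional, either/or analysis. That is a stated choice, not an omission.

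On size, the main analyses carry the last observation forward for everyone with at least one outcome after treatment. The number analysed can therefore exceed 37, which favours the smaller gains at 50. A wide spread of baseline severity would also tend to raise ρ, which again points to the lower end of the gain.

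A reader might infer that randomisation is simple and unblocked, so that imbalance is likely. The article describes random numbers from a spreadsheet and states no blocking or stratification, but this silence does not show that there is none.

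**Conclusion.** The point holds as a worthwhile improvement to the primary analysis. It is not an error that invalidates the plan. The t-test on change gives up 15% to 35% of variance that baseline adjustment would recover, and it leaves about 1.8 to 2.8 points in the estimate for a 1-SE baseline imbalance at 37 per group. These figures rest on an assumed ρ of 0.7 to 0.3, equal variances, and 20 being the SD of change. The practical gain in power is clear at 37 per group, modest at 50 and negligible at 100, so it depends on the unresolved enrolment figure. The gain in precision does not.

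Three stronger readings are not supported:
- That the t-test is biased or inflates the type I error: randomisation protects it on both counts.
- That the primary result will be chosen among models after imbalance is seen: the primary test is named, and the other models are additional.
- That leaving out centre costs a known amount: the article gives no centre effect, so that gain cannot be computed and may be small.

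**What to change.** Name as primary the treatment difference in week-8 SCORAD adjusted for baseline SCORAD by prespecified ANCOVA. The week-8 contrast of a baseline-adjusted repeated-measures model would serve equally well. Keep the unadjusted t-test on change as a supporting analysis. Centre may be added as a second prespecified covariate, since the article states no stratification by centre and leaves the numbers per centre open, but this is a suggestion only.

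Reconcile the two enrolment statements at the same time, because they determine how much power the change buys. The sample size need not change: the existing calculation is conservative for the adjusted analysis under the assumptions above. The cost is a sentence or two in the analysis section, with no new data, visits or participants.
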